## Abstract

**Background:**

Many cancer survivors experience physical and/or psychosocial problems affecting return to work (RTW) and work retention. Current interventions on RTW lack evidence regarding effectiveness, while interventions for work retention are missing. Partners of cancer survivors may also experience work- and health-related outcomes; yet, these consequences are not well understood. Here, the protocol of the STEPS study is described. The study aims are to: 1) evaluate the (cost-)effectiveness of a rehabilitation program for RTW and work retention in cancer survivors, and 2) assess health- and work-related outcomes among cancer survivors’ partners.

**Methods:**

In a multicentre Randomized Controlled Trial (RCT), 236 working-age cancer survivors with an employment contract will be randomly allocated to a usual care group or an intervention group receiving a multidisciplinary rehabilitation program, combining occupational therapy facilitating work retention (e.g., energy management and self-efficacy training) and reintegration consultation addressing work-related issues (e.g., RTW planning and discussing workplace or task modifications with the supervisor). Alongside the RCT, a prospective cohort study will be conducted among cancer survivors’ partners (*n* = 267). Participants in the RCT and cohort study will be asked to complete questionnaires at baseline, and after six and 12 months, assessing work- and health-related outcomes. Generalized estimating equations will be used to assess intervention’s effectiveness, compared to usual care, regarding primary (i.e., working hours per week) and secondary outcomes. Also economic and process evaluations will be performed. For the cohort study, logistic or linear regression modelling will be applied assessing work- and health-related outcomes (primary outcome: working hours) of cancer survivors’ partners, and what factors predict these outcomes.

**Results:**

The study is planned to start in September 2021; results are expected in 2023.

**Conclusion:**

Compared to usual care, the STEPS intervention is hypothesized to be (cost-)effective and the intervention could be a valuable addition to standard care helping cancer survivors to sustain employment. Further, it is expected that living with a cancer survivor has a substantial impact on work and health of partners, while specific groups of partners that are at particular risk for this impact are likely to be identified.

**Trial registration:**

Dutch Trial Register (NTR;NL9094; 15-12-2020).

**Supplementary Information:**

The online version contains supplementary material available at 10.1186/s12889-021-11865-8.

## Background

In the Netherlands, roughly 118,500 individuals are newly diagnosed with cancer each year (https://www.iknl.nl/en/ncr), with approximately 40–50% being of working age. Although 64% will return to work (RTW) after their diagnosis [1], many cancer survivors experience long-term psychosocial (e.g., feelings of depression, anxiety, uselessness and loneliness), physical (e.g., fatigue, pain, nausea, menopausal symptoms and movement limitations), and/or cognitive difficulties (e.g., changes in ability to multitask and working memory), possibly affecting their working lives [2, 3]. Despite these difficulties, work-related care is often not or not systematically provided to cancer survivors [4]. In this study we define cancer survivorship as ‘a process that begins at the moment of diagnosis and continues through the balance of life’ [5].

In the past decades, various interventions have been developed or suggested to support RTW in cancer survivors, including single-component psycho-educational, physical, and medical interventions, and multi-component interventions, such as physical exercise, biofeedback-assisted behavioural training, patient consultation and education, and/or vocational consultation [6]. To date, only weak evidence is available stating that multi-component interventions improve (time to) RTW in cancer survivors, with no evidence supporting the effectiveness of single-component interventions on RTW. Moreover, the majority of evidence is derived from studies conducted in breast cancer survivors, which poses a problem for generalization to other cancer diagnoses and treatment sequelae. Further, while most studies have focussed on RTW after cancer, only few have addressed retention of paid employment beyond RTW. In a recent study among Japanese male cancer survivors, 80% had successfully retained work 1 year after RTW [7]. However, this percentage dropped to 49% after 5 years. Previous studies showed that work retention rates vary significantly with cancer type, with the highest drop-out rates after initial RTW in survivors of lung, liver, pancreas, and oesophageal cancer [7]. Findings from a systematic review showed that 73% of long-term cancer survivors that were working at time of diagnosis managed to retain work 2 years after their diagnosis [8]. Yet, a recent study has shown that many cancer survivors wish to receive work-related care early after diagnosis in the hospital setting, with only few cancer survivors actually receiving such early care [4]. These studies illustrate the difficulty of RTW and retaining paid employment, beyond initial reintegration at the workplace, for cancer survivors. However, few early intervention studies have been conducted to prevent adverse work outcomes and support work retention in cancer survivors [1, 9].

Recently, sustained employment (i.e., RTW and work retention) has been conceptualized as a health *behaviour*, i.e., something a person does or does not do, and that is, to some degree, changeable [10]. Behavioural change models, such as the Stages of Change model [11], have been applied to the development of lifestyle interventions in cancer survivors (e.g., for smoking cessation [12]). A relatively new phenomenon in the scientific community is the application of this model to interventions for sustained employment in cancer survivors [13, 14]. It is theorized that cancer survivors move through several stages of behavioural change regarding RTW and work retention (i.e., pre-contemplation, contemplation, preparation: self-evaluative, preparation: behavioural, uncertain and proactive maintenance) in a non-linear manner (i.e., they can skip stages or lapse back to prior stages) [10]. By identifying a cancer survivor’s behavioural change stage, interventions to support sustained employment can be tailored to better fit the individual’s circumstances [10]. Interventions can therefore be tailored to cancer survivors ranging from those who are starting to consider RTW to those who have already returned to work and are looking to retain work. Providing cancer survivors with a tangible overview of their current stage within the employment trajectory might create a sense of acknowledgment and normalcy, and thereby encourage them to see the bigger picture and formulate work-related goals. The concept of readiness for RTW (RRTW) [15] builds on the Stages of Change model [11] to describe motivational factors contributing to and maintaining behaviour change in the context of sustained employment [15]. Prior research has shown that cancer survivors view the determination of ‘work readiness’ as an important step in the RTW process, and would like to receive guidance in this from health care professionals early on in their illness-trajectory [16]. Recently, Nielsen and colleagues conducted a qualitative study amongst Danish cancer survivors and, again, found that ‘becoming ready’ is a process cancer survivors would like to receive guidance in [17]. To date, however, the application of the Stages of Change model [11] in an intervention to support RTW or work retention has been trialled in some studies (e.g. [18]), but has not been thoroughly explored in cancer survivors.

Contrary to the work-related outcomes of cancer survivors, relatively little is known about the health- and work-related outcomes of cancer survivors’ *partners* (i.e. those who are married to or cohabit with a cancer survivor). It has been reported that the fear of losing their significant other can cause an increase in distress, anxiety and depressions among cancer survivors’ partners [19]. Veenstra and colleagues found that partners of breast cancer survivors reported a negative impact on their financial status, employment status, and health care insurance [20]. These feelings were more pronounced if partners had the financial responsibility for their family, and the majority of partners reported that it was very important to stay in their current job to maintain health insurance. With different social and health care systems, such effects may differ between countries. For example, in the Netherlands, one is obliged to have health care insurance, which is unrelated to having paid employment. There is, however, both globally and in the Netherlands, a lack of knowledge on the work- and health-related outcomes of partners of cancer survivors.

From the above it follows that: 1) work is important for many cancer survivors and their partners, 2) interventions to support RTW in cancer survivors showed limited effectiveness so far, 3) work retention in cancer survivors (beyond initial RTW) is often underrepresented in studies, 4) the Stages of Change model appears a promising angle for interventions aimed at supporting sustained employment of cancer survivors, and 5) little is known about the work- and health-related outcomes of partners of cancer survivors. Therefore, based on identified limitations, the SusTained Employability in cancer Patients and their partnerS (STEPS) study was developed, consisting of:
a multi-centre Randomized Controlled Trial (RCT) to assess the (cost-)effectiveness of the STEPS intervention to support sustained employability (RTW and work retention) in cancer survivors. STEPS is a multidisciplinary intervention that combines the expertise of occupational therapists and reintegration consultants to support RTW and work retention in cancer survivors. STEPS is offered relatively early (i.e., 3–18 months) post-diagnosis to cancer survivors who had an employment contract at time of diagnosis and who are at work or (partly) on sick leave at the time of inclusion.a prospective cohort study to assess work- and health-related outcomes in partners of cancer survivors and identify what factors predict these outcomes.

In this paper the rationale for and protocol of the STEPS study will be described.

## Methods

### Design and setting

The STEPS study consists of a multi-centre RCT to assess the (cost-)effectiveness of an intervention to support RTW and work retention, and a prospective cohort study into the work- and health-related outcomes of partners of cancer survivors. See Fig. 1 for a full overview of the study procedures, which are described in more detail below. The study will be executed by researchers of Amsterdam UMC (location VUmc) and has been approved by its Medical Ethical Committee (reference no. **2020.055).** All procedures will be in accordance with the ethical standards of this local ethics committee and with the Helsinki Declaration of 1975, as revised in 2000. The study has been registered at the Dutch Trial Register (registration no. NTR NL9094; registration date 15-12-2020; https://www.trialregister.nl/trial/9094). Substantial modifications to the protocol will be registered in the trial register (of which an audit trial will be held) and will be disclosed to the local Medical Ethical Committee.

**Fig. 1 Fig1:**
[figure not shown]
Overview of the study procedures, including recruitment, screening and inclusion. NCR = Netherlands Cancer Registry

#### RCT among cancer survivors

This protocol was written according to standard protocol items for clinical trials (SPIRIT) guidelines [21]. The (cost-)effectiveness of the STEPS rehabilitation program will be tested in a multi-centre, two-armed RCT among cancer survivors who are currently receiving, or have recently completed, oncological treatment in one of the participating academic and general hospitals throughout the Netherlands (Supplementary file 1). Eligible cancer survivors will be randomly allocated to the intervention group (receiving the STEPS program) or control group (receiving usual care) and will be asked to complete questionnaires prior to randomization (T0), and after six (T1) and 12 months (T2) follow-up.

#### Cohort study among partners of cancer survivors

In the cohort study, partners of cancer survivors (among others, partners of cancer survivors who participate in the aforementioned RCT) will be recruited. All included partners will be asked to complete questionnaires regarding their work and health at baseline (T0), and at six (T1) and 12 months (T2) follow-up.

### Participants and recruitment

#### RCT among cancer survivors

Cancer survivors of working age (18–63 years at time of diagnosis), with histologically confirmed cancer and a life expectancy of more than 1 year will be recruited. At study entry, eligible cancer survivors have a fixed or temporary employment contract, with at least 6 months left of their contract, and a history of paid work for at least 1 year prior to diagnosis (with ≥8 contracted working hours per week). Cancer survivors can both be at work or (partly) on sick leave when entering the study. Cancer survivors will be recruited 3–18 months post-diagnosis. The cut-off for the maximum time post-diagnosis was set at 18 months for cancer survivors to be able to complete the intervention (with a maximum duration of 6 months) before a potential work disability assessment. According to Dutch legislation, work disability assessments take place after two years of sick leave to determine whether someone is disabled for work or not and may receive work disability benefits or not. Regardless of the outcome of the work disability assessment, employers are allowed to terminate the employment contract after 2 years of sick leave. Moreover, cancer survivors will be eligible for participation in STEPS if they are, or have been, treated with at least radiotherapy and/or chemotherapy. Previous research has shown that cancer survivors who received complex treatments, i.e., chemotherapy, radiotherapy, or a combination thereof, indicated lower work ability than cancer survivors who were treated with surgery alone [22]. Cancer survivors with additional treatment modalities, besides radiotherapy and/or chemotherapy, will be eligible for participation as well.

Cancer survivors will be excluded if their treating physicians consider work unfeasible, if cancer survivors have serious cognitive or psychiatric problems, or other comorbidities that would preclude them from participating in the intervention program, and/or if cancer survivors lack basic proficiency in Dutch. Cancer survivors participating in concurrent studies or rehabilitation programs aimed at sustained employment, or cancer survivors who refuse the involvement of their employer in the STEPS intervention will also be excluded.

#### Cohort study among partners of cancer survivors

Partners are defined as being married to or cohabiting with a cancer survivor who participates in the aforementioned RCT. Cancer survivors and partners of survivors will be recruited independently of each other (and will not be jointly analysed). This means that both partners of cancer survivors who do and do not participate in the RCT will be eligible to participate in the cohort study. Partners of cancer survivors who have had a cancer diagnosis no more than 24 months ago and who have a life expectancy of at least 1 year, are eligible. Partners should be registered at the same address as the cancer survivor at least 1 year pre-diagnosis. Moreover, eligible partners should be between 18 and 65 years of age, have a fixed or a temporary employment contract at the time of diagnosis of the cancer survivors, and a history of paid work for at least 1 year prior to diagnosis (with ≥8 contracted working hours per week). Partners of cancer survivors can both be at work or (partly) on sick leave when entering the study. Partners will be excluded in case of self-reported serious cognitive or psychiatric problems that would prevent them from completing the questionnaires, and/or in case they are unable to understand and complete questionnaires in Dutch.

### Study procedures

#### RCT among cancer survivors

The main route of identification of potentially eligible cancer survivors is through the Netherlands Cancer Registry (NCR). Data managers of the NCR will develop a query based on (a selection of) aforementioned inclusion/exclusion criteria supplied by the researchers. The query will be performed once retrospectively (3–18 months), and prospectively every 3 months for 1 year. The list of potentially eligible cancer survivors will be sent to the involved medical specialist of a participating hospital, who will check whether these cancer survivors are indeed potentially eligible for participation. All potentially eligible cancer survivors will receive an information package with an invitation letter on behalf of the involved medical specialist of the participating hospital, an information brochure, a screening informed consent form, a screening questionnaire and a non-response answer card. If interested, cancer survivors will be asked to sign the screening informed consent form, complete the screening questionnaire and send these documents to the researchers. Cancer survivors will be asked to take a legally mandatory reflection period of at least 1 week before agreeing to participate. Survivors who are not interested in participating can complete a short non-response answer card on which they can indicate their reasons of non-response.

Cancer survivors who meet the inclusion criteria based on the screening questionnaire, will receive a telephone call from a research assistant during which they will be further informed about the project, in- and exclusion criteria will be confirmed, and they will have the opportunity to ask questions. If the cancer survivors’ eligibility is confirmed, they will be asked to sign a second informed consent form for study participation, and subsequently to complete the baseline questionnaire. Upon return of the completed baseline questionnaire, randomisation will take place.

Next to identification via the NCR and recruitment through hospitals, cancer survivors will be recruited through social media channels and (e-mail) messages of the Dutch Federation for Cancer Patient Organizations (NFK), Kanker.nl (a Dutch platform for cancer survivors), and psychosocial oncology walk-in centres (Instellingen PsychoSociale Oncologie; IPSO). Cancer survivors can contact the research team if they wish to receive aforementioned information package. This package will then be sent via post, after which the recruitment procedure is identical to that described above.

#### Cohort study among partners of cancer survivors

Partners of cancer survivors will be invited to participate in the cohort study through the cancer survivors who received an information package regarding the RCT. An invitation letter, information brochure, informed consent form, screening questionnaire and non-response answer card will be included in a separate package, which the cancer survivor (if applicable) may hand over to his/her partner. Partners will be asked to take a legally mandatory reflection period of at least 1 week before agreeing to participate. If a partner is interested, (s) he is asked to sign the informed consent form and complete the screening questionnaire, based on which eligibility will be checked. Upon request partners are given the opportunity to ask questions about the study in a telephone call. Partners who are not interested in participating can complete a short non-response answer card on which they can indicate their reasons of non-response.

Additional recruitment pathways (similar to the one for cancer survivors described above) consist of social media and e-mail messages through NFK, Kanker.nl, and IPSO walk-in centres.

### Sample size calculation

#### RCT among cancer survivors

The RCT sample size calculation is based on the primary self-reported outcome measure, i.e., working hours per week. Based on previous research [23], a standard deviation of 13 h per week was assumed, and a between group (intervention versus control) effect of 5.5 h per week is expected. Given this effect size, with a power of 80% and level of statistical significance set at *p*-value< 0.05, the sample size required is 88 cancer survivors in each group (176 in total). In this study 236 cancer survivors will be recruited, to allow for an attrition rate of approximately 25% (i.e., cancer survivors who discontinue participation in the study entirely, including failure to complete the follow-up questionnaires) and to enable subgroup analyses.

#### Cohort study among partners of cancer survivors

Because of the lack of literature on work- and health-related outcomes of partners of cancer survivors, the sample size calculation is based on the secondary objective of the cohort study, i.e., identifying factors to predict partner’s work- and health-related outcomes. A generally accepted formula was used to estimate the sample size [24], i.e., *n* = 10 observations per variable in the smallest outcome group. Hence, to generate the prediction model with a maximum of 10 variables a sample size of at least *n* = 100 in the smallest outcome group is required. As the ratio of partners with positive and negative work- and health-related outcomes is expected to be 50:50, a total sample size of *n* = 200 is required. About 267 partners will be recruited, to allow for an attrition rate of approximately 25%.

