#### Cohort study among partners of cancer survivors

The primary outcomes for partners are working hours per week and health-related quality of life. Secondary outcomes include change in working hours (as a percentage of the contract hours at baseline), ‘employment status’ (at work/not at work), sick leave, health-related work functioning, caregiver burden and depression. Information on a number of additional parameters (see Table 1 for a full overview) will be gathered to describe the study sample and/or as predictors in the prediction model.

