#### Cohort study among partners of cancer survivors

Reason of non-response before baseline (from the answer card) and during the follow-up period will be tabulated to get a better understanding of the representativeness of our sample. The distribution of baseline values of primary and secondary outcomes and additional variables will be described. The longitudinal nature of the data enables examination of the course of primary and secondary outcome measures over time in partners, using GEE for longitudinal data with time as independent variable and the outcome variables as dependent variables.

A time lag prediction model will be used to determine which characteristics predict the primary outcomes in partners of cancer survivors [48]. In this time lag model, the measurements of the predictors will be related to outcomes status 6 months later, thus relating baseline (T0) predictors to outcomes at T1, and predictors at T1 to outcomes at T2 [51]. Univariate analyses with *p* < 0.10 will be conducted, to select possible relevant predictors. Continued selection on the remaining predictors from the univariate analyses will be based on multi-collinearity and accepted in the multivariate GEE analyses if correlation coefficients are ≥ − 0.7 and ≤ 0.7 [52].

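### Partner cohort: the sample size basis (binary outcome, at most 10 variables) does not match the planned prediction model, and uncapped univariate screening leaves that model open to overfitting

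*Protocol article*

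**What the plan says.** All references are to the Protocol article.

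- **Sample size calculation, partner cohort.** The size is based on the secondary (prediction) objective. The rule is "10 observations per variable in the smallest outcome group", so that "to generate the prediction model with a maximum of 10 variables a sample size of at least" 100 in that group is needed. The step to a total is: "As the ratio of partners with positive and negative work- and health-related outcomes is expected to be 50:50", hence 200. Then: "About 267 partners will be recruited, to allow for an attrition rate of approximately 25" per cent.
- **Measurements, partner cohort.** "The primary outcomes for partners are working hours per week and health-related quality of life". The additional variables in Table 1 may serve to describe the sample, to act as predictors, or both. Table 2 lists working hours and the SF-12 t-score as continuous and gives no cut-off for either.
- **Statistical analyses, partner cohort.** "A time lag prediction model will be used to determine which characteristics predict the primary outcomes in partners of cancer survivors". Predictors at T0 are related to outcomes at T1, and predictors at T1 to outcomes at T2. Univariate analyses at p < 0.10 "will be conducted, to select possible relevant predictors". Those that pass enter a multivariable GEE unless pairwise correlations fall outside ±0.7.
- **Abstract, Methods.** Logistic or linear regression is named for the cohort.

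**The concern.** Two separate things do not fit together.

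First, a rule that counts the smaller outcome group needs a two-category outcome. The outcomes named as targets of the prediction model have no categories, so the 50:50 split has nothing to refer to.

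Second, the sizing assumes a model of at most 10 variables, but the analysis section does not carry that limit forward. A p < 0.10 screen and a collinearity filter leave the number of predictors to the data. Selection in the same data also uses up information for every candidate tested, not only for those kept, so the relevant count is the candidate pool.

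At stake is whether the reported predictors and their coefficients would hold up in other partners. The Discussion intends the results to help tailor support for partners, so optimistic coefficients and noise predictors would matter.

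**Working it through.** **1. The plan's own figure.** 10 variables × 10 per variable = 100 in the smaller group; 100 / 0.5 = 200 completers; 200 / 0.75 = 266.7, i.e. 267. Both stated figures reproduce.

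**2. Outcome scale.** The sizing needs a dichotomy. The model's named targets are continuous in Table 2. Employment status and depression are dichotomous there, but both are secondary outcomes for partners, and the prediction paragraph names only the primary outcomes.

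**3. Size of the candidate pool.** The plan gives no number, so this is a count from Table 1. The partner column has 31 rows marked as additional variables with measurement times. Splitting age/gender, education/income and company size/sector gives 7 sociodemographic + 4 medical + 3 lifestyle + 2 health + 8 employment + 10 work = 34. Work ability is also marked as additional for partners but has no time points; including it gives 35.

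Parameters exceed variables. On Table 2's categories, cancer site (17 plus other), sector (13 plus other) and marital status (9 options) alone need 17 + 13 + 8 = 38. Coding the rest as listed, with one parameter wherever the categories are not spelled out, gives at least 19 + 20 + 8 + 3 + 24 + 11 = 85 in the same six groups.

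**4. Partners per candidate, continuous outcome, 200 completers.**

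- Planned 10 variables: 200 / 10 = 20
- 34 candidate variables: 200 / 34 = 5.9
- 85 parameters: 200 / 85 = 2.4

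The two lagged intervals give at most 400 outcome observations. They are correlated within partner, so the effective number lies below that. Even at the ceiling, 400 / 34 = 11.8 per variable.

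**5. Does it matter?** This depends on the true R², which the document does not give, so a range is assumed. The n needed for an expected shrinkage factor S = 0.90 with p parameters is n = p / ((S − 1) ln(1 − R²/S)). Example: 34 / (−0.1 × ln(1 − 0.2/0.9)) = 34 / 0.02513 = 1353.

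A simulation of the stated procedure used n = 200, one outcome per partner, 34 candidates of which 5 are true predictors, and pairwise correlation 0 or 0.2. Every candidate with univariate p < 0.10 entered a linear model. The ranges below cover the two correlations.

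| True R² | n, 10 parameters | n, 34 parameters | Calibration slope in new data (34 candidates) | Apparent R² | R² in new data |
|---|---|---|---|---|---|
| 0.2 | 398 | 1353 | 0.71–0.78 | 0.26–0.27 | 0.10–0.12 |
| 0.3 | 247 | 839 | 0.75–0.89 | 0.34–0.39 | 0.19–0.24 |
| 0.5 | 124 | 420 | 0.84–0.97 | 0.53–0.58 | 0.40–0.46 |
| 0.7 | 67 | 227 | 0.92–1.00 | 0.71–0.75 | 0.64–0.68 |

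At correlation 0.2, about 25 to 34 candidates passed the screen over this range of R², well above 10, and a ±0.7 filter would remove none of them. With uncorrelated candidates, about 7 to 8 passed. With only 10 candidates and R² = 0.2, the slope was about 0.88.

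**The case against.** The strongest reply has four parts.

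- **The pool is not fixed at 34.** The Measurements section does not commit every additional variable to prediction, and a condensed article may leave the candidate list and the validation method to a fuller document. This stands: 34 is an upper-range count, and the absence of a list or of a validation step is not in itself the point. What remains is in the text: the stated selection rule can draw on a pool far larger than 10, and nothing in it applies the stated cap.
- **Continuous outcomes are more favourable than the binary rule implies.** This also stands. A reader might infer that the mismatch itself causes overfitting, or might divide the binary group of 100 by 34 and report 2.9 per candidate. Neither is supported. With 10 variables, 200 completers give 20 per variable, and the figure for the whole pool is 5.9.
- **Repeated observations help.** They do, somewhat, and the table leaves them out. Even 400 independent observations would fall short of 839 and 1353, the numbers for 34 parameters at R² of 0.3 and 0.2.
- **The abstract allows logistic regression.** It does, but no cut-off for working hours or SF-12 is given anywhere, so the 50:50 split still has no defined outcome.

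A reader might also infer that 267 partners cannot be found because the RCT enrols 236 survivors. The Participants section also admits partners of survivors outside the RCT, so the target is not limited in that way.

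**Conclusion.** The point holds in a limited form. The arithmetic behind 200 and 267 is correct, but its basis matches no prediction analysis described for the primary outcomes. Separately, the univariate screen is uncapped and can draw on about 31 to 35 variables.

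That the model is bound to be overfitted is not supported. The outcome depends on the true R², on how many candidates are actually screened and on how they correlate, none of which is given. If the whole pool is screened with about 200 completers, the risk is substantial at R² of about 0.3 or less: at 0.2, the R² in new data is less than half the apparent value. It is intermediate at 0.5 and small near 0.7. These results rest on the simulation's assumptions of five true predictors, correlation 0 to 0.2 and one parameter per variable. Multi-category variables would make matters worse; the second lagged interval would ease them.

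The point concerns the cohort's secondary, predictive objective only.

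**What to change.** 1. Replace the univariate p < 0.10 screen with one of two options:
   - candidates chosen in advance on subject-matter grounds, using at most 10 parameters in total (not 10 variables), with sparse categories such as cancer site and sector pooled, all fitted together; or
   - a penalised model over all candidates.
2. In either case, report bootstrap optimism-corrected performance, resampling partners rather than single observations, and apply shrinkage to the coefficients.
3. Restate the sizing for continuous outcomes: 200 completers / 10 parameters = 20 per parameter. Remove the reference to a smallest outcome group and a 50:50 split. Do not claim that 20 per parameter alone rules out overfitting: at R² = 0.2, 10 parameters would need 398 for a shrinkage factor of 0.90, repeated intervals not counted. This is why step 2 is needed under the first option too.

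**Cost.** Wording and analysis only; no extra recruitment and no change to the RCT. The first option examines fewer candidate predictors. The second means slightly more analysis work and may need software beyond the SPSS version named for all analyses.
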